**Figure 1 F1:**
[figure not shown]
Flow chart of study protocol.

### Study registration

2.2

The protocol scheme matches PRISMA's reporting standards. This study protocol has been registered on Chinese Clinical trial registry (http://www.chictr.org.cn/index.aspx) with an ID of ChiCTR2000030075.

### Participants

2.3

A total of 1000 cases of neonatal hyperbilirubinemia were diagnosed in the full-term neonatal ward of Xiamen Children's Hospital from March 2020 to September 2020.

#### Inclusion criteria

2.3.1

The inclusion criteria are as follows:

1.Newborn ≤ 28 days, gestational age > 35 weeks, weight ≥ 1.8 kg;2.Apgar score >7 points at 1 minute, 5 minutes, and 10 minutes after birth;3.Neonatal who were first diagnosis as hyperbilirubinemia, not combined with elevated bilirubinemia, will receive the physical audiometry. Hearing screening was completed within 48 hours after admission: distortion product otoacoustic emission (DPOAE) and automatic auditory brainstem response (AABR) were applicable for hearing screening.

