**Methods and analysis::**

A total of 1000 children with hyperbilirubinemia who are mainly indirectly elevated bilirubin in the full-term neonatal ward of Xiamen Children's Hospital from March 2020 to September 2020 will be enrolled. Using second-generation high-throughput sequencing technology, 127 deaf-related genes were sequenced from the collected samples. At the same time, physical audiometry was performed on the selected persons and audiometry data were recorded.

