#### Diagnostic criteria for neonatal hyperbilirubinemia

2.3.3

According to the 2004 American academy of pediatrics guidelines for neonatal jaundice intervention, neonatal hourly bilirubinemia is defined as hyperbilirubinemia when bilirubin levels exceed the 95th percentile

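### Inclusion criterion 3 cannot be applied as written, and gestational age and weight should enter the bilirubin–hearing model whatever the univariate screen shows

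*Protocol article*

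**What the plan says.** Section 2.3.1 gives three inclusion criteria. The first sets age, maturity and weight: "Newborn ≤ 28 days, gestational age > 35 weeks, weight ≥ 1.8 kg". The third concerns the diagnosis: "Neonatal who were first diagnosis as hyperbilirubinemia, not combined with elevated bilirubinemia, will receive the physical audiometry".

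Section 2.3.3 gives the diagnostic rule: "neonatal hourly bilirubinemia is defined as hyperbilirubinemia when bilirubin levels exceed the 95th percentile". It does not say whether total, direct or indirect bilirubin is meant. The exclusion list in section 2.3.2 does not mention direct bilirubin or cholestasis. The only hint about the fraction is in the abstract, which describes the children as those "who are mainly indirectly elevated bilirubin in the full-term neonatal ward".

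Full-term occurs only as a description of the recruiting ward, in the abstract and in section 2.3: "A total of 1000 cases of neonatal hyperbilirubinemia were diagnosed in the full-term neonatal ward". It is not defined in weeks, and no criterion requires term birth.

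The Introduction names preterm birth and low birth weight among the common risk factors for neonatal hearing loss. Section 2.5, item 3, models the audiometry result by binary logistic regression, using as independent variables those that were significant in univariate analysis, with P < .05 as the level.

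**The concern.** An eligibility rule has to sort infants into those who qualify and those who do not. Criterion 3 cannot, because its two halves exclude each other under the protocol's own definition. Whoever applies it must supply a missing qualifier, and the document does not settle which. The gap affects the exposure: the Introduction and Discussion both make the relation of serum and unbound bilirubin to hearing impairment an object of the study. If one reader admits infants with a raised direct fraction and another does not, they are studying different conditions under one name.

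The second issue is smaller. The eligibility rules remove several of the risk factors listed in the Introduction: low Apgar scores, asphyxia and hypoxic injury, intracranial infection, and ototoxic drugs. Immaturity and low weight are limited by criterion 1 but not removed. Whether the analysis adjusts for them then depends on a significance screen.

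**Working it through.** No sample-size, power or event figure bears on this point, so there is no figure of the plan to reproduce. The check sets the sections side by side.

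**Step 1: criterion 3 against the definition.**
- Section 2.3.1, criterion 3, first half: the infant has hyperbilirubinemia.
- Section 2.3.3: hyperbilirubinemia means bilirubin above the 95th percentile, which is elevated bilirubin.
- Section 2.3.1, criterion 3, second half: the infant does not have elevated bilirubin.

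The first two lines together deny the third. The criterion is coherent only if the second half refers to a different quantity from the first.

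**Step 2: does another section supply that quantity?**
- The abstract points to indirect bilirubin, so the second half may concern the direct fraction. But the abstract is a description with no threshold, and its qualifier (mainly) leaves open whether mixed elevation is allowed.
- Section 2.3.3 names no fraction.
- Section 2.3.2 excludes no direct or cholestatic disease.

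The intended meaning can be guessed but not established, and the status of an infant with a raised direct fraction is undetermined.

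**Step 3: maturity and weight.**
- Criterion 1 admits gestational age above 35 weeks and weight from 1.8 kg.
- Assumed cut-offs, not in the document: 37 weeks for term and 2.5 kg for low birth weight.
- Admitted below the term cut-off: above 35 and below 37 weeks, a band of 37 − 35 = 2 weeks.
- Admitted below the weight cut-off: 1.8 kg to below 2.5 kg, a band of 2.5 − 1.8 = 0.7 kg.
- Criterion 1 says weight, not birth weight, in infants up to 28 days old. The match with the Introduction's risk factor is therefore approximate.
- The document does not say how many of the 1000 infants fall in these bands.

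**Step 4: what the model does with them.** Under section 2.5, item 3, gestational age and weight enter only if each is significant on its own. A listed risk factor that misses P < .05 in this sample is dropped, although a non-significant univariate result does not show that adjustment is unnecessary.

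**Step 5: which analysis is affected.**
- Bilirubin and hearing: maturity and weight are listed risk factors for the outcome. The document does not say whether they are also related to bilirubin level in this cohort, so confounding is possible but not shown.
- Genotype and hearing: confounding would need gestational age or weight to be associated with the inherited variants. The document gives no reason to expect that.

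**The case against.** The strongest reply is that criterion 3 contains a slip of wording or translation, that the abstract shows what was meant, and that no clinician would be misled. It is fair that the slip would not in practice empty the study. A reader might infer that nobody is eligible, but that treats a drafting fault as an enrolment result. What remains is that the abstract's phrase is not an eligibility rule and carries no limit. A condensed article may leave an operational cut-off to a fuller document. Here, however, the rule is stated, and stated in a form that contradicts section 2.3.3.

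A reader might also infer that "gestational age > 35 weeks" contradicts the term full-term, so that the enrolled population is not the one named. The documents do not support that. Section 2.3 says only that cases "were diagnosed in the full-term neonatal ward", which describes a ward, and the two statements are compatible if the label is simply the ward's name. The 37-week limit comes from outside the document. This objection stands, and only a request for a clearer description survives it.

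Third, covariate lists and sensitivity analyses commonly belong in an analysis plan that is not shown. That holds for a term-only sensitivity analysis, which is therefore optional. It does not fully answer the adjustment point, because section 2.5 does state how covariates are chosen, and that rule can discard risk factors the protocol itself names.

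Finally, the Introduction speaks of risk factors and does not claim that each acts as an independent cause. The argument for adjustment needs no more than that.

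**Conclusion.** The point holds on criterion 3: read with section 2.3.3 it contradicts itself, and the abstract, section 2.3.2 and section 2.3.3 do not settle whether infants with a raised direct fraction are in or out. This rests on the text alone. Its numerical effect cannot be stated, because the document does not say how many infants have a raised direct fraction.

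The label full-term is not shown to conflict with the gestational-age limit. The population should nevertheless be described by the limit actually used, so that readers do not take the ward's name for a restriction to term births.

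The adjustment point holds as an improvement to the model of bilirubin and hearing impairment. It assumes the usual cut-offs of 37 weeks and 2.5 kg, and that some infants in those bands are recruited; their share is unknown. It does not extend to the comparison of genotype with hearing, and it does not show that any result would be biased.

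**What to change.** 1. Restate criterion 3 so that it names the bilirubin fraction that must not be elevated and gives the threshold the sponsor intends. Make the abstract and section 2.3.3 agree, including which fraction the 95th percentile refers to. The choice of fraction and threshold is the sponsor's. This costs a wording correction.

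2. Describe the population by its gestational-age limit, and say that full-term refers to the ward if that is what is meant. This costs one sentence.

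3. In section 2.5, item 3, enter gestational age and weight into the logistic model of bilirubin and hearing impairment regardless of their univariate P values, and say whether weight means birth weight. Both are needed to check criterion 1, so no new data are required.

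The price of item 3 is two extra model terms. As a rough guide, if the 2% to 4% that the Introduction quotes for hearing impairment in high-risk newborns applied here, 1000 × 0.02 = 20 to 1000 × 0.04 = 40 infants would be affected. The rate of abnormal audiometry in this cohort is not given and may differ. With numbers of that order, each variable is best entered as a single continuous term.

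4. Optionally, repeat the model in term infants only, with the definition of term stated. This costs one additional analysis.

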**Discussion::**

In this study, we will combine gene sequencing with clinical indications of hyperbilirubinemia to find the loci suitable for high-frequency pathogenic deafness related to hyperbilirubinemia, so as to provide early guidance for deafness gene screening in children with hyperbilirubinemia.

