## Introduction

1

Congenital hearing impairment is the most common congenital disease, with an incidence of about 0.1% to 0.3% in healthy newborns and as high as 2% to 4% in high-risk newborns.^[1]^ The most common risk factors for neonatal hearing loss include central infection, neonatal sepsis, hyperbilirubinemia, perinatal asphyxia and hypoxic encephalopathy, preterm delivery, low birth weight, low Apgar score, prolonged mechanical ventilation, and ototoxic agents. Children with hyperbilirubinemia whose serum total bilirubin level reached the blood exchange indicator are one of the common risk factors for hearing loss in children with Neonatal intensive care unit (NICU).^[2]^ The mechanism of hyperbilirubinemia on auditory impairment is not clear. Some scholars believe that hearing loss is a prominent manifestation of bilirubin neurotoxicity.^[3]^ The brain stem auditory pathway is particularly sensitive to the toxic effect of bilirubin.^[4,5]^ High bilirubin levels can even cause permanent damage to nerve development, mainly including deafness and infant cerebral palsy.^[6,7]^

This study protocol will explore the occurrence characteristics of hearing impairment in neonatal children with hyperbilirubinemia, the relationship between serum bilirubin level, unbound bilirubin and the occurrence of hearing impairment, the mutation characteristics of deafness gene in children with hearing impairment, and the difference between deafness gene and normal population.

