### Data collection

2.4

Neonatal patients (1000 cases) diagnosed with hyperbilirubinemia were selected, and 2 ml of blood was collected from the selected persons. Using second-generation high-throughput sequencing technology, 127 deaf-related genes were sequenced from the collected samples. At the same time, physical audiometry was performed on the selected persons and audiometry data were recorded. Genetic test data and physical audiometry data were correlated and analyzed to find the pathogenic loci of hyperbilirubinemia susceptibility to deafness. For those patients with definite symptoms of hyperbilirubinemia and deafness, and no pathogenic loci were detected in 127 genes, blood was collected from these patients, and total exon sequencing was performed to analyze about 22,000 genes and find new pathogenic loci.

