### Statistical plan

2.5

Excel was used to establish the database, and SPSS 22.0 statistical software was used for statistical analysis in this study.

1.Continuous variable data: for continuous variable data conforming to normal distribution or approximate normal distribution, mean ± standard deviation was adopted to describe the comparison of inter-group differences. When data of continuous variables do not follow normal distribution or variance is uneven, it is expressed as median (quartile spacing) M (P25, P75). Wilcoxon rank sum test in non-parametric test is performed, and multi-independent sample test is performed when there is statistical significance.2.Categorical variables data were described as adoption rate or composition ratio of. Chi-square test was used for comparison of differences between groups, and *P* < .05 was considered statistically significant.3.Logistic regression analysis: physical audiometry results were taken as the dependent variable, and indicators with statistical significance of univariate analysis results were taken as independent variables for binary logistic regression analysis. *P* < .05 was considered as a statistically significant difference.4.ROC curve analysis.

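### The only hearing measure described is a DPOAE/AABR screen within 48 hours of admission; a refer on it does not support a conclusion about deafness loci

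*Protocol article*

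**What the plan says.** - **Measurement.** Under 2.3.1 Inclusion criteria: "Hearing screening was completed within 48 hours after admission". The tests follow: "distortion product otoacoustic emission (DPOAE) and automatic auditory brainstem response (AABR) were applicable for hearing screening". Infants may be up to 28 days old. No repeat screen, diagnostic test or later audiology is described anywhere in the article.
- **Model.** Under 2.5 Statistical plan, "physical audiometry results were taken as the dependent variable", and the indicators that were significant in univariate analysis "were taken as independent variables for binary logistic regression analysis". No pass/refer definition is given, and no rule for using two tests as one binary outcome.
- **Interpretation.** Under 2.4 Data collection: "Genetic test data and physical audiometry data were correlated and analyzed to find the pathogenic loci of hyperbilirubinemia susceptibility to deafness". The Abstract states the goal as to "find the loci suitable for high-frequency pathogenic deafness related to hyperbilirubinemia".
- **Mechanism.** The Introduction says: "The brain stem auditory pathway is particularly sensitive to the toxic effect of bilirubin".

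**The concern.** The measurement is a screen taken close to admission for jaundice; the conclusion is about pathogenic deafness. A refer at that moment can mean at least three things: lasting hearing loss, dysfunction from the current bilirubin load that later resolves, or a false refer in an infant with normal hearing. The Introduction itself treats lasting damage as something high bilirubin can cause, not as its only effect. No step in the plan separates the three.

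Two things are at stake. First, if true impairment is uncommon, even a small false-refer rate fills the case group with infants who are not impaired. Where those refers are unrelated to genotype, odds ratios shrink toward 1 and real loci may be missed. Second, a locus that does reach significance could be called a correlate of a screening refer, but not a deafness locus.

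There is a secondary gap. The Introduction places the bilirubin effect in the brain stem pathway, so it matters which of the two tests gave the refer. The Statistical plan names one dependent variable and does not say how the two results enter it.

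**Working it through.** The article states 1000 infants without a derivation, event rate or effect size, so there is no figure of its own to reproduce. The check asks what the stated outcome would contain.

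**Inputs**
- N = 1000 (2.3 Participants).
- Prevalence of true impairment, prev = 2% to 4% (Introduction, high-risk newborns).
- Sensitivity, se = 95%: assumed.
- False-refer rate among unimpaired infants, f = 1% to 10%: assumed. It counts any refer without true impairment, including transient dysfunction.

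**Step 1: make-up of the case group**

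True refers = N × prev × se. False refers = N × (1 − prev) × f. False share = false / (true + false).

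| prev | f | true | false | false share |
|---|---|---|---|---|
| 2% | 1% | 1000 × 0.02 × 0.95 = 19 | 980 × 0.01 = 9.8 | 9.8 / 28.8 = 34% |
| 4% | 1% | 1000 × 0.04 × 0.95 = 38 | 960 × 0.01 = 9.6 | 9.6 / 47.6 = 20% |
| 2% | 5% | 19 | 980 × 0.05 = 49 | 49 / 68 = 72% |
| 4% | 5% | 38 | 960 × 0.05 = 48 | 48 / 86 = 56% |

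So f between 1% and 5% gives a false share between 20% and 72%. At f = 10% it is 72% (prev 4%) to 84% (prev 2%).

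**Step 2: effect on a genotype association**

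Further assumptions: 20% of truly impaired infants and 5% of the others carry the variant, and false refers do not depend on genotype. The true odds ratio is (0.20/0.80) / (0.05/0.95) = 4.75. Take prev = 3%, so there are 28.5 true refers and 1.5 missed cases.

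For f = 5%:
- False refers = 970 × 0.05 = 48.5, so there are 77 refers and 923 passes.
- Carriers among refers = (28.5 × 0.20 + 48.5 × 0.05) / 77 = 10.6%.
- Carriers among passes = (1.5 × 0.20 + 921.5 × 0.05) / 923 = 5.0%.
- Observed odds ratio = 2.23 (from the unrounded proportions).

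| f | observed OR | power, one locus, two-sided 0.05 |
|---|---|---|
| no misclassification | 4.75 | 0.82 |
| 2% | 3.06 | 0.68 |
| 5% | 2.23 | 0.53 |
| 10% | 1.73 | 0.37 |

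**Step 3: does the text repair this?**
- Data collection refers to patients whose deafness is definite. That wording selects who goes on to exome sequencing; it names no confirmatory test and does not enter the regression.
- Exclusion criteria (2.3.2) remove abnormal middle ear function. That may remove some false refers, but not transient neural dysfunction or chance refers.

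**The case against.** **Acute dysfunction can be a legitimate target.** The Introduction and Discussion list as aims the occurrence of hearing impairment in these newborns and its relation to serum and unbound bilirubin. For those aims an acute refer is not misclassified. This stands, and it confines the point to the deafness-locus conclusion.

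**The condensed article may omit follow-up.** The 48-hour sentence sits among the inclusion criteria, the flow chart is not shown, and a later test is not ruled out. A reader might infer that hearing is certainly measured only once; the article shows only that no other test is described. Even so, the timing, tests, dependent variable and interpretation are written down and do not fit together. If confirmatory testing exists elsewhere, these sections still need to be aligned with it.

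**Merging the tests is not stated.** A reader might infer that DPOAE and AABR are collapsed into one result. No combination rule is written, and one model per test is compatible with the text. What can be said is that the outcome is left open between two tests.

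**The sizes rest on assumptions.** The article gives no refer rate, false-refer rate, sensitivity or carrier frequency, and requiring a refer on both tests would lower f. This stands: the figures show direction and plausible scale, and are not properties of this study. Nor do the documents support applying the Introduction's healthy-newborn incidence to this cohort, which would give a far more extreme attenuation.

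**One test pattern as a marker of bilirubin injury.** A reader might go on to claim that an AABR refer with a DPOAE pass best separates bilirubin injury from genetic cochlear loss. The article supports only brain stem sensitivity and does not say where genetic loss acts.

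**Conclusion.** The point holds in this form: the only hearing measure described is a screen within 48 hours of admission, its result is the binary dependent variable, and the association is then read as evidence on deafness. That outcome does not support a deafness-locus conclusion.

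For scale, 1000 infants at the article's 2% to 4% impairment range, with assumed 95% sensitivity and an assumed 1% to 5% false-refer rate, would give about 20% to 72% false refers among those counted as cases. An illustrative odds ratio of 4.75 at 3% prevalence would be observed as 2.23 at a 5% false-refer rate. The attenuation requires false refers to be unrelated to genotype. Its direction does not depend on the exact rates.

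The interpretive problem needs none of these numbers, because it follows from what was measured and when. The lack of a rule for the two tests is a lesser, related gap.

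**What to change.** - **2.5 Statistical plan.** Model AABR refer and DPOAE refer as separate outcomes, and tabulate the joint DPOAE-by-AABR pattern. Include age and bilirubin at the time of the test as adjustment variables, whether or not they pass the univariate screen.
- **Abstract and 2.4 Data collection.** Name the endpoint *hearing-screen refer during acute hyperbilirubinemia* and limit conclusions to it. Reserve deafness, including in the definition of the exome-sequencing subgroup, for infants with confirmed loss where such a result exists.

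The cost is some rewording and one extra model, since both tests are already planned. The price is a more modest claim and fewer events per outcome. Separating the tests does not itself remove false or transient refers or restore an attenuated odds ratio; the restricted conclusion does the main work.

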#### Exclusion criteria

2.3.2

The exclusion criteria are as follows:

1.Family history of deafness;2.History of birth anoxia, neonatal asphyxia;3.Plane malformation, abnormal middle ear function;4.Neonatal intracranial infection, intracranial hemorrhage, neonatal hypoxic-ischemic brain injury;5.History of cytomegalovirus infection and fever during pregnancy, history of ototoxic drugs, and mother's congenital nervous system history of disease;6.Further exclude those with incomplete clinical data.

#### Diagnostic criteria for neonatal hyperbilirubinemia

2.3.3

According to the 2004 American academy of pediatrics guidelines for neonatal jaundice intervention, neonatal hourly bilirubinemia is defined as hyperbilirubinemia when bilirubin levels exceed the 95th percentile

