## Discussion

3

Neonatal hyperbilirubinemia is one of the common diseases in neonatal period, especially in the first week after birth, accounting for about 50% to 75%.^[8]^ Most children have no long-term adverse effects, but hyperbilirubinemia is one of the most important risk factors for hearing loss.^[9]^ To identify and intervene the hearing loss caused by neonatal hyperbilirubinemia timely, effectively, safely, and economically in the early stage, and to reduce unnecessary treatment and waste of medical resources are the efforts of the medical community at home and abroad for many years.

Central infection, neonatal sepsis, hyperbilirubinemia, perinatal asphyxia and hypoxic-ischemic encephalopathy, preterm delivery, low birth weight, and other risk factors for neonatal hearing loss have a much higher incidence of hearing loss than common children.^[10–12]^ What are the mechanisms by which these risk factors contribute to hearing loss? Could it be that something is causing a mutation in the deafness gene that causes deafness? There are few related researches at home and abroad, which is the problem that this study aims to solve. This study protocol will explore the occurrence characteristics of hearing impairment in neonatal children with hyperbilirubinemia, the relationship between serum bilirubin level, unbound bilirubin and the occurrence of hearing impairment, the mutation characteristics of deafness gene in children with hearing impairment, and the difference between deafness gene and normal population.

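### Serum bilirubin, the exposure of a stated objective, enters the logistic model only if it passes a univariate test, and the plan neither relates its level to age nor identifies infants at exchange level

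*Protocol article*

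**What the plan says.** The Introduction of the protocol article, repeated in its Discussion, makes the following an objective: "the relationship between serum bilirubin level, unbound bilirubin and the occurrence of hearing impairment".

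Section 2.3.3 defines a case by an age-specific cut: "neonatal hourly bilirubinemia is defined as hyperbilirubinemia when bilirubin levels exceed the 95th percentile". Section 2.3 gives the cohort: "A total of 1000 cases of neonatal hyperbilirubinemia were diagnosed in the full-term neonatal ward".

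Section 2.5 compares continuous variables between groups, by the Wilcoxon rank sum test when they are not normal. It then builds a binary logistic model with the audiometry result as outcome, by this rule: "indicators with statistical significance of univariate analysis results were taken as independent variables for binary logistic regression analysis". The threshold is P < .05. ROC analysis is listed without naming a variable.

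On where the hearing risk lies, the article says two things. The Introduction states: "Children with hyperbilirubinemia whose serum total bilirubin level reached the blood exchange indicator are one of the common risk factors for hearing loss", speaking of NICU children. The Discussion attaches no threshold: "hyperbilirubinemia is one of the most important risk factors for hearing loss". The Introduction's general list of risk factors also names hyperbilirubinemia without a level.

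**The concern.** When an objective is the relationship between one exposure and an outcome, that exposure should be estimated and reported whatever a preliminary test shows. Under section 2.5, bilirubin can drop out before the model is fitted, leaving no adjusted estimate and no interval for a stated objective.

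Two features make the screen weak for this exposure. First, entry depends on the infant's age in hours, so two infants equally far above their own thresholds can have quite different raw values. A test on raw level carries that age variation as noise. Second, the one level that the Introduction singles out, the exchange indicator, is not carried into the analysis as a grouping. If risk is concentrated in a small upper tail, a rank test across the whole range is a poor detector of it.

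At stake is a non-significant screen being taken as evidence that bilirubin level does not matter, when the screen had little chance of showing that it does.

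**Working it through.** **The plan's own figure.** The 1000 comes with no effect size, event rate or power, so there is nothing to reproduce.

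**Inputs from the article.** n = 1000 (section 2.3); alpha 0.05 (section 2.5, taken as two-sided); hearing-loss rates of 0.1% to 0.3% in healthy newborns and 2% to 4% in high-risk newborns (Introduction).

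**Assumptions, none of them in the article.**
- Risk is a step: 4% at or above exchange level, 0.3% below it. The article gives its 2% to 4% for high-risk newborns in general, not for this level.
- The share q of enrolled infants at exchange level is 5%, 10% or 20%.
- Raw bilirubin = age-dependent entry level (SD 3) + excess over that level (exponential, mean 2). Exchange level is the top share q of the excess.

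**Expected impaired infants** = 1000 × [q × 0.04 + (1 − q) × 0.003]:
- q = 5%: 2.0 + 2.85 = 4.85
- q = 10%: 4.0 + 2.7 = 6.7
- q = 20%: 8.0 + 2.4 = 10.4

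**Why raw level is noisy.** The variance of the entry level is 3² = 9 and that of the excess is 2² = 4. Only 4/13 = 31% of the variance of raw bilirubin then reflects severity.

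**Simulated power at P < .05** (repeat runs moved these figures by up to about 3 points):

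| Test | q = 5% | q = 10% | q = 20% |
|---|---|---|---|
| Rank-sum, raw level | 25% | 37% | 47% |
| Logistic score test, raw level | 34% | 43% | 51% |
| Rank-sum, age-corrected excess | 32% | 60% | 89% |
| Linear test, age-corrected excess | 61% | 77% | 89% |
| Fisher, exchange level yes/no | 58% | 81% | 96% |

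Most of the gain comes from relating bilirubin to age and from not using a rank test. Once both are done, the split adds little: 58% against 61%, 81% against 77%, 96% against 89%.

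**Sensitivity.**
- *Fewer events.* Fisher power is 28% at a 2% share with 0.3% and 4%. With 0.2% and 3% it is 24% at a 2% share and 47% at a 5% share. The split does not cure a shortage of events.
- *Commoner outcome.* The outcome may be a screening referral, whose rate the article does not give. With assumed rates of 5% and 15%, rank-sum on raw level has 16%, 32% and 54%, and Fisher has 71%, 92% and 99%.
- *Smooth risk.* With log-odds rising linearly in the excess and q = 5%, the yes/no comparison has 95% and the rank-sum test on age-corrected excess 96%. Little is lost by leaving exchange level unseparated.

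**The case against.** A reader might infer that the article places the hearing risk only at exchange level, enrols too low, and so dilutes the relationship. The documents do not support that. The exchange-indicator sentence describes one common risk factor among NICU children. Elsewhere the Introduction and the Discussion name hyperbilirubinemia as a risk with no threshold. Entry above the 95th percentile contradicts neither statement. It also supplies the lower-level infants without whom a relationship with level could not be estimated. The Discussion's 50% to 75% ("especially in the first week after birth, accounting for about 50% to 75"%) is background on how common the condition is, not the population to which results will be applied. These points stand.

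It also stands that the step-shaped risk and the exchange-level share are assumed, and that applying the healthy-newborn rate to infants above the 95th percentile is a strong assumption. A condensed article may leave subgroup detail to the full protocol or analysis plan, so the lack of an exchange-level stratum is not in itself an error. Whether NICU infants are covered is largely answered, since recruitment is stated as the full-term neonatal ward.

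The entry rule is different, because section 2.5 states it. Logistic regression on bilirubin cannot rescue a variable that the screen has already removed. ROC analysis, listed without a variable, keeps nothing in the model. The article does not say that a non-significant screen will be reported as no relationship; the point is that the stated rule leaves the objective without a model estimate in that case.

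**Conclusion.** The point holds as a minor one. The stated selection rule can remove the exposure of a stated objective, and raw level is a blunt measure because case definition depends on age. That needs no assumption about where the risk lies.

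How much power is lost is conditional. If risk is concentrated at exchange level, with 0.3% and 4% and shares of 5% to 20%, the rank-sum screen on raw level would drop bilirubin in about 75% to 53% of such studies (100 − 25 and 100 − 47). Age-corrected linear testing would miss it in about 39% to 11% (100 − 61 and 100 − 89). At smaller shares or lower rates every method has low power. If risk rises smoothly, separating exchange-level infants gains little. The article shows neither that the relationship is diluted nor that its entry criterion is wrong.

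**What to change.** In section 2.5:

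1. Keep serum bilirubin in the logistic model whatever its univariate P value, expressed relative to the infant's age-specific threshold, and report its odds ratio with a 95% CI.
2. Alongside it, report the number of infants and the impairment rate with exact 95% CI by whether the infant reached the exchange indicator, and compare the two groups with an exact test. Classify infants without knowledge of the hearing result, and name the indicator meant: the Introduction mentions one but gives no values.
3. State that a non-significant univariate test will not be read as absence of a relationship.

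The cost is one derived variable and one more reported comparison. Section 2.4 does not list bilirubin and age in hours among the data collected, but the diagnosis in section 2.3.3 requires both, so the sponsor need only confirm that they are kept in the database. Enrolment and clinical care are unchanged.
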